#### Intervention Tool

In this study, tasks run on Montessori educational wooden toys—cylinder socket blocks (32). There are 40 wooden cylinders and four sets of wooden socket blocks in total, 10 each per group and each a cylinder with varying widths and depths as same as the corresponding wooden socket block. All cognitive tasks commence with verbal instruction from the trained researcher regarding how to use the socket cylinder and what are the tasks involved. The trained researcher will receive 10 h of training and an intervention manual containing a simplified version of the cognitive training task with illustrations. Participants who fail to complete the task within the set time will be given proper technique guides, but the researchers will not help them complete the tasks.

#### Difficulty Level

The difficulty level, rounds, and progression of cognitive training will be individualized (33). There are 8 levels of difficulty in cognitive training, and 64 same difficulties in each level (except for the task of Stereoscopic cylinders training and Hunt for the colors). The completion time or error frequency of three consecutive training sessions are less than 80% compared with the first attempt, and the training difficulty level will increase. In contrast, the completion time or error frequency of three consecutive training sessions are better than 50% compared with the first attempt, and the training difficulty will decrease. The completion time or error frequency of three consecutive training sessions are 50% to 80% compared with the first attempt; the training difficulty level will increase conversely; the training difficulty level will remain unchanged. Besides, to maintain the challenge and maximize performance, the participants who have not increased the difficulty level for three consecutive weeks will be required to attempt a higher level of difficulty. Each task is presented first at its simplest level, and each subsequent task is a variation of previously mastered skills as the complexity increases.

#### Control Intervention

Participants in the control group are on the waiting list and will receive 10 weeks of health education classes twice a week, at 40~60 min per session. The wait-list group will access to attend the same after the group had completed a 3-month follow-up. The items of health education included the disease knowledge of MCI, physical activity, cognitive activities and social activity. Participants were reminded via smartphone to complete their training program if missing over 2 weeks.

#### Study Procedure

Participants will be enrolled from the nearby community health service centre via open recruitment through paper flyers, online forums, and word-of-mouth. Participants who interested in this program will be invited for an in-person interview to complete a screening questionnaire in the community health service centre, including demographic characteristics, MMSE, MoCA, ADL, and Achromatopsia anomalous trichromatic test (AATT). A trained physician in community health service centre will invite the potential participants to undergo a physical examination and neurologic diagnosis of MCI. Participants who met the eligibility criteria will be assessed with a baseline assessment and then given the EEG evaluation in the 2 days preceding the start of the cognitive training.

After that, according to the random allocation sequence, participants will be randomly assigned to one of two groups with a targeted assignment ratio of 1:1. The random allocation sequence with a block size of four will be generated using a computer randomization list by an independent researcher assistant. The random allocation sequence is sealed in opaque envelopes by an assistant. The cognitive training group will receive cognitive intervention and health education, whereas the wait-list control group will only receive health education during the research period. During the 3 months follow up, the cognitive training group and wait-list control group will receive no interventions. Complete all outcome assessments, participants in the wait-list control group will be permitted to undergo the process-based multi-task cognitive training program. Although it was not initially the plan, the health education manual for mild cognitive impairment will be provided for participants who are not finishing the cognitive training or health education through various means, such as email, public platform, and short messaging service. All outcome measurements will be assessed at baseline, 10 weeks and 3 months follow up. Study assessments and timelines are illustrated in **Table 3**.

**Table 3 T3:** Summary of study assessments and timelines.

Time point	Measurement	Post-allocation					Mode of Administration
		Baseline	Training sessions	10 weeks assessments		Follow-up 3 months	
		T0		T1		T2	

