**Methods:**

This program is a single-blinded, randomized, prospective clinical trial to test the effect of process-based multi-task cognitive training in older adults with MCI. Ninety participants with MCI will be recruited and randomly assigned to the cognitive training group (n=45) and the wait-list control group (n=45). The cognitive training group will receive 10 weeks of process-based multi-task cognitive training and health education twice a week, at 40~60 min per session. While the wait-list control group will only receive 10 weeks of health education during the research period. The effect is measured using the executive function, neuropsychological assessment performance and related brain activity assessed with electroencephalogram parameters (slowness and complexity of the EEG) at baseline, after 10 weeks of training, and a 3-month follow-up.

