### Study Intervention

#### Implementation of the Cognitive Training Program

Participants in the cognitive training group will receive 10 weeks of the process-based multi-task cognitive training program with 60 min group training sessions (a small group of six participants) each given three times per week. This cognitive training program consisted of eleven training tasks in total, with a varying degree of overlap between tasks. The tasks are divided into three categories: 1) warm-up exercise; 2) practice in order; and 3) expanding training (**Table 2**). The task of warm-up exercise lasting 10 min, practice in order and expanding training tasks lasting 50 min. All cognitive tasks are completed within a medical university setting supervision of postgraduate in Master of Nursing Specialist. The program ensures that the ratio of a participant-to-researcher is no greater than 6:1 (6 participants per researcher). Each training task for all nursing specialists was randomly assigned. During the training period, the participant will have an identical training schedule. To balance the social-interaction effect, participants in the cognitive training group participated in the same health education program as the wait-list control group. Participants were reminded via smartphone to complete their training program if missing over 2 weeks. Besides, we develop a training paper record form, and the training record can be checked.

**Table 2 T2:** Tasks of process-based multi-task cognitive training program.

Categories	Tasks	Targeted domain	Difficulty levels/rounds	number of hours	A brief description of the tasks
Warm-up exercise	Recall the names	Memory	0/20	10min	Firstly, introduce yourself one by one (i.e., name, age, occupation). Then, inform participants to remember these names. The participants are asked to write down the names of the other five on white paper according to their memory at the end of cognitive training.
	You act I guess	Working memory	0/1		Firstly, participants were divided into three groups of two. Then, one participant facing the audience uses the most accurate body language to express the meaning of words, while other participants with their backs to the audience are asked to guess those words. Each group is limited to 2 min.

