## Trial Status

The study is currently ongoing. Recruitment began in March 2019 and will conclude at the end of 2020.

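### A single published block size of four, with arms visibly different on delivery, lets anyone who follows earlier allocations in order deduce up to one third of assignments

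*Protocol article*

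**What the plan says.** The protocol article, under Study Procedure, gives the allocation method in three statements:

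- Ratio: "participants will be randomly assigned to one of two groups with a targeted assignment ratio of 1:1". No stratification factor is named, so the text implies one list.
- Generation: "The random allocation sequence with a block size of four will be generated using a computer randomization list by an independent researcher assistant". One size is given, with no mention of variation.
- Concealment: "The random allocation sequence is sealed in opaque envelopes by an assistant".

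Other parts of the article bear on how much an observer could learn:

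- Eligibility is settled before allocation, partly on clinical judgement: "A trained physician in community health service centre will invite the potential participants to undergo a physical examination and neurologic diagnosis of MCI" (Study Procedure). Baseline testing and EEG also come before allocation, with the EEG in the two days before training starts.
- The arms differ in what is delivered: "the wait-list control group will only receive health education during the research period" (Study Procedure), while the other arm has the cylinder-block training as well.
- Training takes place away from the recruiting centre: "All cognitive tasks are completed within a medical university setting supervision of postgraduate in Master of Nursing Specialist" (Implementation of the Cognitive Training Program). It is given in groups of six.
- The Abstract says "This program is a single-blinded, randomized, prospective clinical trial". Outcome Measurement describes both the evaluators and the training staff as masked.
- Trial Status says "Recruitment began in March 2019 and will conclude at the end of 2020", so the block size was published with recruitment still open.

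**The concern.** In a fixed block, the last assignments follow from the earlier ones. This matters when past assignments can be seen, and here they can be seen on delivery, because one arm handles cylinder blocks in small groups and the other attends classes only. The statement that training staff are masked offers no protection, since people who deliver training to one arm know which arm it is.

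The decision to enrol someone, and its timing, both come before allocation. If the person making that decision can predict the next arm, more motivated or less impaired people could be directed to one arm. The planned repeated-measures ANOVA (Statistical Considerations) cannot remove selection on characteristics that were not measured. Baseline testing also comes before allocation, so an assessor who expects a particular arm could influence the baseline from which change in executive function is judged.

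**Working it through.** The article gives no predictability figure to reproduce, so the figures below are derived from its design.

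**Inputs.** Block size 4 and ratio 1:1 (Study Procedure). Total 92 in the sample-size paragraph, which is 92/4 = 23 complete blocks. The Abstract gives 90, which is 90/4 = 22.5 blocks.

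**Conditions assumed for the observer.** Knows the block size, knows where each block begins, and knows every earlier assignment in order.

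**Certain assignments.** A 1:1 block of four has six equally likely orders.
- In 2 of the 6 (AABB, BBAA) the last two assignments are determined.
- In the other 4 only the last is determined.
- Expected number per block = (2 × 2 + 4 × 1)/6 = 8/6 = 1.33, and 1.33/4 = 33.3%.
- Over 92 participants: 23 × 1.333 = 30.7.
- With the Abstract's 90: the first two places of a block are never certain, so 22 × 1.333 = 29.3.

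**Best guess.** The observer always names the under-represented arm and tosses a coin when the block is level.
- AABB type: 0.5 + 0 + 1 + 1 = 2.5 correct.
- The other four orders: 0.5 + 1 + 0.5 + 1 = 3 correct.
- Expected = (2 × 2.5 + 4 × 3)/6 = 17/6 = 2.833 of 4 = 70.8%, against 50% with no information.

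**Without earlier assignments.** If the observer does not know the earlier assignments, no assignment is certain (0%).

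**What one known arm reveals.** Of the other three members of the block, two are in the opposite arm. Each is therefore opposite with probability 2/3, and none is determined. Certainty needs two known members in the same arm, or three known members in total.

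**Effect of other block sizes.** The fixed sizes were enumerated exactly. The varying sizes were simulated (2,000 trials of 92) for an observer who knows every earlier assignment and the set of sizes, but not the size of each block.

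| Scheme | Certain | Best guess correct |
|---|---|---|
| Fixed 4 | 33.3% | 70.8% |
| Fixed 6 | 25% | 68.3% |
| Fixed 8 | 20% | 66.6% |
| Varying 4/6 | 5.5% | 69% |
| Varying 2/4/6 | 4.0% | 70% |
| Varying 4/6/8 | 2.4% | 68% |

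Varying the sizes removes most of the certainty but little of the guessing advantage. If a whole cohort is enrolled before any of its assignments is made, and each cohort is balanced by itself, earlier allocations carry no information for any enrolment decision.

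**The case against.** The case on the other side has real force in several respects.

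- **One third is a ceiling.** It needs someone who chooses whom to enrol and who also follows every earlier assignment in order. Screening is at the community centre and training is at a medical university under other staff. Nothing in the article says that recruiters see past allocations. This stands, and the figure has to be read as a maximum.
- **Allocation may already happen in batches.** Training groups of six starting together would suggest about 12 people allocated at about the same time, which is three complete blocks. Those people would be enrolled before any assignment in their blocks was visible. This is possible, but the article states neither batch nor one-by-one allocation.
- **Entry is partly numeric.** The MMSE and MoCA limits and the 1.5 SD criterion on Logical Memory leave less room for steering than judgement alone would. This also stands, but the physician's diagnosis and the timing of enrolment remain open.
- **A fixed block of four is conventional, and an article may leave masking of recruiters to the full protocol.** That is fair for who opens the envelopes. It does not cover the block size, which the article itself fixes and publishes.

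Two stronger readings are tempting. A reader might infer that concealment cannot be relied on. The text does not support that, because it describes an independently generated list and sealed opaque envelopes and shows no route by which recruiters learn past arms. A reader might also infer that an evaluator who learns one participant's arm thereby knows others in the block. In a block of four, one known arm determines no other.

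**Conclusion.** The point holds as a weakness in concealment, not as a demonstrated failure of it. A single published block size of four, with arms that can be told apart on delivery, makes at most 33.3% of assignments certain (about 31 of 92) and allows 70.8% correct guesses. Both figures assume that the observer knows the block boundaries and every earlier assignment. The article does not establish how far anyone involved in enrolment meets those conditions, and the true exposure may be much lower, down to no certain assignments at all. Envelopes do not remove the risk, because the deduction uses earlier assignments rather than the sealed card. No misuse is alleged. The change is worth making because the bias it guards against cannot be repaired in the analysis and the cost is small.

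**What to change.** For allocations not yet made, in order of preference:

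1. **Randomise complete cohorts.** Close a cohort (for example 12 people, 6 per arm, which matches the training groups of six) once all are confirmed eligible and have completed baseline. Then assign the whole cohort in one step. Cost: a new list, and a short wait for each cohort to fill. The last cohort may be smaller. If the whole target of 92 were split this way, 92 = 7 × 12 + 8, so it would have 4 per arm.
2. **Otherwise, vary the block size.** Have the independent assistant regenerate the list with randomly varying, undisclosed sizes, for example 4, 6 and 8. This cuts certain assignments to about 2%, but best-guess success only to about 68%. Cost: a new list, re-packed envelopes and a possible final imbalance of a few participants.

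Under the second option, keep block sizes and past assignments from recruiters and evaluators. Under either option, state in the protocol who opens the envelopes and that those deciding on enrolment do not see earlier assignments. Record the date and participant number at which the method changed.

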**Enrollment**							
**Eligibility screening**							Paper and pencil
**Informed consent**							Paper and pencil
**Screening**	**General information**						
	Demographic information						Paper and pencil
	**Daily functions**						
	Activities of Daily Living (ADL)						Observation
	**Optic examination**						
	Achromatopsia anomalous trichromatic test						Paper and pencil
	**Neuro psychological examination**						
	Mini–Mental State Examination (MMSE)						Paper and pencil
	Montreal cognitive assessment (MoCA)						Paper and pencil
**Randomized allocation**							
**Intervention**							
**Training tasks**	**↔**					
Warm-up exercise	**√**						Paper and pencil
Practice in order	**√**						Cylinder socket blocks
Expanding training	**√**						
**Assessments**							
**Primary objective**	**Executive function**						
	Trail Making Test A-B	**√**		**√**		**√**	Paper and pencil
	Color-Word Matching Stroop task	**√**		**√**		**√**	Computer
	Purdue pegboard test (Model 32020A)	**√**		**√**		**√**	Device
**Secondary objectives**	**Overall cognitive function**						
	Montreal Cognitive Assessment (MoCA)	**√**		**√**		**√**	Paper and pencil
	**Psychomotor speed**						
	Finger Tapping test	**√**		**√**		**√**	Device
	Reaction Time test (EP203)	**√**		**√**		**√**	Device
	**Transfer effects**						
	Raven’s Advanced Progressive Matrices	**√**		**√**		**√**	Computer
	Digit span test	**√**		**√**		**√**	Paper and pencil
	**Neuroimaging assessments**						
	Electroencephalogram	**√**		**√**		**√**	Computer

### Outcome Measurement

Data evaluators and training practitioners are blinded to group assignments. All outcome measures are assessed at baseline, immediately after 10 weeks of training, and again at follow-up 3 months after the end of cognitive training. Three trained research assistants, with a minimum of 2 years’ experience conducting mental health nursing and neuropsychological assessments, conducted a set of outcome measures. A more detailed account of study assessments and timelines are illustrated in **Table 3**.

The primary outcome measure is the composite z score executive function, which will be accessed by Trail Making Test A-B (TMT A-B), Stroop test (using software, E-Prime 2.0.10.42), and Purdue pegboard test (PPT, Lafayette Instrument Model 32020A). The selection of cognitive evaluation measures, directly relating to the target cognitive field of training, can improve cognitive training power, efficacy and increase accuracy (34, 35). Furthermore, previous studies have shown that the use of TMT A-B, Stroop tests, and PPT as executive function outcome measures in clinical trials of MCI (36, 37). We will calculate z-score composites from normalized raw data for each item and its score as a sum of all domains.

The secondary outcome measures include neuropsychological assessments, transfer effect and electroencephalogram acquisition. Neuropsychological assessments are as follows: (1) the composite z score for the overall cognitive function, including the questionnaire of MoCA (38); (2) the Psychomotor speed, which will be accessed by Finger Tapping Test (37) and Reaction Time test (39). The transfer effects measure consist of fluid reasoning and working memory. Two tasks will be used to measure working memory: digit span forward and backward from the Wechsler Adult Intelligence Scale-Revised. Raven’s Advanced Progressive Matrices (RAPM) will be used to assess fluid reasoning. The electroencephalogram data will be recorded and collected using the Emotiv EPOC® Headset (EMO-EPO-BT9X-03) with 14 channels mobile (AF3, F7, F3, FC5, T7, P7, O1, O2, P8, T8, FC6, F4, F8, and AF4) and two references (CMS/DRL references at P3/P4; left/right mastoid process alternative). The parameters are as follows: the sampling rate is 128 Hz, the resolution is 14 bits with 1 LSB (= 0.51μV), and bandwidth is 0.16–43Hz (digital notch filters at 50Hz and 60Hz). The recording time will last approximately 5 min. The participants will be required to close and open their eyes for 30 s, respectively. During data acquisition time, the participants will be told not to move their hands and other parts of the body (40).

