The calculation of sample size is based on the change in executive function after 10-week, which is the primary outcome variable in this study. A meta-analysis found that significant benefits of cognitive training are superior to the wait-list and the effect size of executive function training used to calculate the sample size is 0.575 [0.093,1.056] (18, 19). Sample size estimation was conducted using statistical software G*power. In the analysis with an independent t-test using a power of 80% and a type 1 error of 5%, the calculated total sample for this study is 78. Considering a 15% dropout rate and maximum to ensure the credibility of the cognitive training, we will recruit 46 participants in each group. Thus, the total required sample size for this study is 92 participants.

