Practice in order	Match the cylinders	Executive function	1/64	50min	Firstly, take any set of socket cylinder socket*, make the cylinder out of the socket, placed near the corresponding socket block, then throw the order of a group of cylinders into confusion. The participants will be required to place each cylinder into appropriate holes in a long wooden socket block with the left-to-right or the right-to-left order. There are sixty-four cylinder socket combinations. With more socket cylinders and change in combination model shown, the difficulty level increases.
	Match the socket apertures		2/64		Firstly, take any set of socket cylinder socket, make the cylinder out of the socket, placed near the corresponding socket block, then throw the order of a group of cylinders into confusion. A wooden cylinder was selected and placed it into the participant’s hand. The participants will be required to find the corresponding position of each cylinder and place it into appropriate holes in a long wooden socket block. With more socket cylinders and changes in the combination model shown, the difficulty level increases.
	Locate the cylinders		3/64		Firstly, take any set of socket cylinder socket on the table, make the cylinder out of the socket, placed socket block on another table. The participants will be required to select suitable cylinders that were shown in the first group and place each cylinder into appropriate holes in a long wooden socket block with the left-to-right or the right-to-left order according to their memory. With more socket cylinders and changes in the combination model shown, the difficulty level increases.
Expanding training	Recall the cylinders		4/64		The participants will be required to complete a task on level 1 (Match the cylinders) with eyes closed. With more socket cylinders and changes in the combination model shown, the difficulty level increases.
	Recall and locate the cylinders		5/64		The participants will be required to complete a task on level 2 (Match the socket apertures) with eyes closed. With more socket cylinders and changes in the combination model shown, the difficulty level increases.

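### The primary executive-function composite includes a pegboard test that resembles the placement task being trained, so a positive result need not mean a wider executive gain

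*Protocol article*

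**What the plan says.** Under Outcome Measurement, the primary outcome is a composite executive-function z-score from three tests: "Trail Making Test A-B (TMT A-B), Stroop test (using software, E-Prime 2.0.10.42), and Purdue pegboard test (PPT, Lafayette Instrument Model 32020A"). The construction rule is one sentence: "We will calculate z-score composites from normalized raw data for each item and its score as a sum of all domains". The article justifies the choice of measures as "directly relating to the target cognitive field of training" and cites earlier trials in mild cognitive impairment that used these three tests as executive outcomes.

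The Intervention Tool section says that "tasks run on Montessori educational wooden toys—cylinder socket blocks". In Table 2 the basic act is to "place each cylinder into appropriate holes in a long wooden socket block", and the later levels vary it. The Implementation section gives 10 minutes of each session to warm-up and 50 minutes to the practice and expanding tasks. Under Control Intervention, the comparison arm receives health education classes; the training arm receives the same classes plus the training.

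Motor speed has its own place among the secondary outcomes: "the Psychomotor speed, which will be accessed by Finger Tapping Test" and a reaction-time test.

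**The concern.** The primary aim, in the Background, is to find out whether training improves executive function. A pegboard test is one of the components that are added up to answer that question. Only the training arm spends ten weeks handling cylinders and putting them into matching holes, so randomisation cannot separate better manual placement from better executive control. Both would appear as a difference between arms on the pegboard component, and both would pass into the composite.

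At stake is the meaning of a positive primary result. If the pegboard component drives it, the trial has shown that people improve at something close to what they practised. The article would report that as an executive benefit and commend it to community health workers.

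**Working it through.** **How much of the training is placement.** Table 2 lists eight cylinder tasks. Seven have participants put cylinders into fitting holes: levels 1 to 3 directly, levels 4 and 5 by repeating levels 1 and 2 with eyes closed, and levels 6 and 8 by repeating level 1 with coloured cylinders. Level 7 is stacking. These eight tasks fill 50 of the 60 minutes given in the Implementation section (50/60 = 83%).

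**The plan's own sample size.** Inputs from Study Design and Participants: effect 0.575, power 80%, type 1 error 5%, independent t-test, dropout 15%. The noncentral t distribution gives:
- one-sided 5%: 39 per arm, 78 in total, power 0.81; 78/0.85 = 91.8, so 92. This reproduces the stated figures.
- two-sided 5%: 49 per arm, 98 in total. This does not reproduce 78. At 39 per arm the two-sided power is 0.71.

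The article does not state sidedness. The figures below use a two-sided test at 39 per arm, with the one-sided equivalent noted.

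**Assumptions for the composite.** The article gives no component weights, test correlations or expected pegboard gain. I assume three equally weighted z-scores, all aligned so that higher is better, unit variances, a common correlation ρ, and no effect on trail-making or Stroop.

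**Formula.** The variance of the sum of three z-scores is 3 + 6ρ. A gain of g SD on pegboard alone therefore gives a standardised composite effect of

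d = g / √(3 + 6ρ).

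At ρ = 0.3, √(3 + 1.8) = √4.8 = 2.191. The smallest observed d that reaches two-sided significance at 39 per arm is 1.992 × √(2/39) = 0.451.

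| Pegboard-only gain g (SD) | Composite d at ρ = 0.3 | Significant, two-sided | Range for ρ = 0.2 to 0.5 |
|---|---|---|---|
| 0.3 | 0.3/2.191 = 0.14 | 9% | 8 to 10% |
| 0.575 | 0.575/2.191 = 0.26 | 21% | 18 to 23% |
| 1.0 | 1.0/2.191 = 0.46 | 51% | 43 to 57% |

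With the one-sided 5% test that reproduces the planned 78, the three entries at ρ = 0.3 become 15%, 31% and 64%.

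**Sensitivity to the weight.** If the Trail Making Test contributed two scores, giving four equal components, a 1.0-SD pegboard gain would yield 1/√(4 + 12 × 0.3) = 1/√7.6 = 0.36 instead of 0.46.

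**The case against.** The strongest defence is that closeness to training is deliberate and disclosed. The article says that it chose measures close to the trained field, cites earlier trials that used the pegboard test as an executive outcome, and makes generalisation to untrained domains a secondary aim. That stands as a reason not to insist that pegboard leave the primary outcome. It does not remove the confounding: general use of a test as an executive measure says nothing about a trial whose intervention is itself peg-like placement.

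A second objection is that the size rests on unsourced inputs. This is fair. The 51% needs a 1.0-SD gain on pegboard with none elsewhere, a gain nearly twice the planned effect of 0.575. At 0.575 SD the figure is 21%. The equal one-third weight is also an assumption, because the article does not say how many scores each test contributes. Nor does it describe the pegboard procedure; the resemblance is inferred from the nature of a pegboard test and from Table 2.

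A reader might also go further and infer that the composite adds scores running in opposite directions, times on some tests and a count on another, so that gains cancel. The article does not support this. It names no score for any test and does not say that scores are left unreversed. Aligning directions is routine, and an article may leave it to the full protocol or analysis plan. Even in that hypothetical case, with equal component effects and ρ = 0.3, the effect would be diluted from 0.575 to 0.27, not cancelled. Likewise, nothing says that scores are standardised within each visit. If they were, the main effect of time would vanish, but the group-by-time contrast that carries the treatment effect would remain.

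**Conclusion.** The overlap is documented. A pegboard test sits in the summed primary composite, seven of the eight cylinder tasks rehearse placing objects into holes, and the control arm has no such practice. A positive primary result therefore does not by itself establish a wider executive gain.

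The chance that pegboard alone produces a significant result is small for a modest gain (9% at 0.3 SD), about one in five for a gain equal to the planned effect, and about one in two only for a gain of a full SD. These figures hold under equal weights, correlation 0.3, 39 per arm and a two-sided 5% test, and the pegboard gain matters far more than the correlation. They do not show that a positive result would probably be an artefact, or that the composite is invalid. The point is one of interpretation, and it should be settled in the plan before the data are seen.

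**What to change.** Three additions to the definition and analysis of the primary outcome:
1. Pre-specify the trail-making plus Stroop composite, without pegboard, as the key sensitivity analysis of the primary outcome.
2. Report the pegboard result separately and label it a near-training measure.
3. State that a positive primary result will be described as an executive-function effect only if the composite without pegboard points the same way.

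While that text is being written, name the score taken from each test, and state that all z-scores are aligned so that higher is better and are standardised at every visit to the pooled baseline mean and SD. This completes the rule; it does not correct a demonstrated error.

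The cost is wording only. No assessments are added and no sample size changes. The downside is that a two-test composite is slightly less reliable than a three-test one, so the sensitivity analysis should be judged on direction and estimate, not on its own significance.
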